### Objectives and specific aims

The primary objective of our study is to longitudinally track changes in sleep microstructure throughout the ECT course of a convenience sample of patients, who are clinically ascertained and treated for depressive episodes on a busy hospital-based service. Wearable dry-electrode EEG devices will be utilized to monitor overnight sleep at home. High-density EEG during the ECT procedure will allow characterization of seizure markers. Specific aims, hypotheses, and analytical approaches are listed below.

#### Specific aim 1

Assess changes in N2 and N3 sleep SWA over the course of serial ECT sessions. We hypothesize SWA will increase over the course of ECT. Separate linear mixed effects models will be constructed to assess SWA changes in responder and non-responder groups.

#### Specific aim 2

Evaluate changes in sleep spindle density during N2 and N3 sleep over the course of ECT. We predict that there will be an increase in sleep spindle density throughout ECT. Separate linear mixed effects models will be constructed to assess changes in sleep spindle density in responder and non-responder groups.

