**FIGURE 3 F3:**
[figure not shown]
PICOT (participants, intervention, control, outcomes, timing) summary of study design. This study will recruit adults requiring ECT treatment for a depressive episode. Participants will wear a Dreem headband at night to obtain sleep EEG recordings throughout the course of ECT. High-density EEG recordings will also be obtained during ECT sessions to assess central positive complexes (CPCs). The primary outcomes of CET-REM include characterization of slow wave activity and sleep spindle density throughout ECT course.

Each enrolled participant will undergo an index course of ECT, following standard clinical care. Self-reported depressive scores will be assessed prior to each ECT session to determine response, and the total number of treatments will be determined by the psychiatrist performing ECT, as part of routine clinical practice. Response to the ECT will be defined as a 50% reduction of baseline QIDS score. Sleep structure on the nights of ECT sessions would be confounded by the effects of the anesthetic used in the procedure. Thus, ambulatory overnight sleep EEG data will be acquired *via* a Dreem device on post-ECT days. For exploratory analyses, optional high-density EEG data will be recorded during ECT-induced seizures. Our study design will allow us to longitudinally collect a large data set of EEG markers, including sleep slow waves, sleep spindles, and CPCs.

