### Clinical assessments

Two clinical assessments will be done throughout this study, the QIDS-SR16 (Quick Inventory of Depressive Symptomatology-16 Self Report), and the PSQI (Pittsburgh Sleep Quality Index). The QIDS-SR16 measures the participant’s depressive symptoms over the past seven days (86). At our institution, patients receiving ECT typically complete QIDS-SR16 throughout their ECT course. While other scales for measuring depression severity exist, such as Hamilton Depression Rating Scale (HAMD) and Montgomery–Asberg Depression Rating Scale (MADRS), the usage of QIDS-SR16 in the ECT suite has been historically chosen because it is a patient-reported assessment that accommodates for the high volume of participants in the suite limited clinician resources. The questionnaire includes 16 questions that survey nine symptom domains: sad mood, self-criticism, poor concentration, suicidal ideation, anhedonia, energy, sleep disturbance, appetite, and psychomotor agitation. Paper versions of the QIDS-SR16 will be completed by participants prior to each ECT session. The PSQI is a scoring system to assess sleep quality and habits during the past month (87). The assessment measures seven components of sleep: subjective sleep quality, sleep latency, sleep duration, sleep efficiency, sleep disturbances, sleeping medications, and daytime dysfunction. PSQI will be obtained *via* an electronic form administered prior to the first ECT session. Suicidality will be assessed by psychiatry physicians in the ECT suite, as per standard of care.

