### Electroconvulsive therapy

Electroconvulsive therapy will be delivered using standard-of-care clinical protocols. Three stimulation electrode placements will be utilized: right unilateral (electrodes placed on the right temple and vertex of the head), bilateral (electrodes placed on the right and left temple), and bifrontal (both electrodes placed on the forehead, above the outer canthus of the eye).

Prior to ECT stimulation, general anesthesia will be induced. Commonly used regimens include etomidate 0.2 mg/kg, methohexital 1 mg/kg, or ketamine 1.5 mg/kg. The anesthetic regimen will be determined at the anesthesiologist’s discretion. Standard American Society of Anesthesiologists safety monitoring will occur throughout treatment.

The ECT stimulation will be delivered *via* routine clinical practice, using the Thymatron System IV. On the initial treatment (dose titration) session, ECT-naïve individuals typically receive right unilateral ECT titration at 5% charge, 0.3 ms pulse-width, 40 Hz frequency. While a seizure duration of 20–25 s has been accepted to be adequate by some, there are no firm data that support this position. Instead, seizure duration appears to not determine adequacy of response (88–93). Therefore, at our institution seizure duration is not used to determine adequacy of the treatment. Instead, a seizure duration of 10 s is defined as a reasonable minimal limit for determining the presence of an induced seizure. If an appropriate seizure is not obtained after this initial stimulation, then ECT charge will be increased in a protocolized fashion until a seizure of at least 10 s is obtained. Subsequent right unilateral treatments are then administered at a charge sixfold above seizure threshold.

If, based upon the clinical judgment of the ECT clinician, right unilateral ECT at sixfold seizure threshold does not improve depressive symptoms, participants may then transition to 100% right unilateral charge and if need be bilateral ECT at two-times seizure threshold. If during the course of ECT seizure duration becomes less than 10 s, then modifications, based on the exact clinical situation will be made by the ECT psychiatrist in how ECT is provided in order to increase duration to above 10 s.

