### Statistical analysis

Linear mixed-effects models will be constructed to account for missing data without the need for data imputation or deletion. Models will be generated in MATLAB. To characterize SWA over the course of ECT, linear mixed-effect models will be constructed using SWA as a dependent variable and treatment number as an independent variable. Similarly, to examine sleep spindle density changes, linear mixed-effects models will be generated that have sleep spindle density as a dependent variable and treatment number as an independent variable. Associations between CPC and sleep SWA or sleep spindles will be evaluated *via* respective linear mixed-effect models. For all aims, separate models will be constructed for responder and non-responder groups. QIDS-SR16 scores and ECT stimulation *parameters* will be entered as covariates for all analyses, as appropriate.

A total number of 25 participants will be targeted for recruitment in this study. Sample size calculations are based on the published data following conventions for statistical power analysis in the behavioral sciences (100) and our best guesses regarding effect size and SD. The main factor that we considered in estimating our required sample size was based on reported changes in SWA measure in major depression (98, 101, 102). We estimate a medium effect size and a partial η^2^ value of 0.1. Thus, we estimate sample sizes of 17 (power of 0.8, alpha of 0.05) based on a conservative assumption on the number of treatments (10 treatments) to account for missing a session or poor quality of EEG data. Participants may withdraw from the study at any time, and we will track reasons for patient attrition. Given that a previous study on a similar patient population cohort conducted at Barnes-Jewish Hospital and Washington University showed a 30% attrition rate (80), we expect to have at least 17 participants with interpretable data in the current study.

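### The covariate rule reaches the Aim 1 and 2 slope models: if per-session QIDS is entered, treatment number no longer estimates total change over the ECT course

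*Protocol article*

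**What the plan says.** All places are in the protocol article.

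- **Target (Objectives and specific aims).** Aim 1: "We hypothesize SWA will increase over the course of ECT". Aim 2: "We predict that there will be an increase in sleep spindle density throughout ECT". Both concern the overall change across the course.
- **Models (Statistical analysis).** For Aim 1, "linear mixed-effect models will be constructed using SWA as a dependent variable and treatment number as an independent variable". For Aim 2, the models "have sleep spindle density as a dependent variable and treatment number as an independent variable". Responders and non-responders are modelled separately.
- **Covariates (same section).** "QIDS-SR16 scores and ECT stimulation *parameters* will be entered as covariates for all analyses, as appropriate". The text does not say whether the QIDS value is the baseline or the per-session score, or what decides when a covariate is appropriate.
- **QIDS (Clinical assessments).** "Paper versions of the QIDS-SR16 will be completed by participants prior to each ECT session". Sleep disturbance is one of its nine symptom domains.
- **Responder groups (Study design, after the Figure 3 legend).** "Response to the ECT will be defined as a 50% reduction of baseline QIDS score".
- **Stimulation (Electroconvulsive therapy).** Settings can change during the course. If symptoms do not improve, "participants may then transition to 100% right unilateral charge and if need be bilateral ECT at two-times seizure threshold".
- **Mechanism (Abstract, Introduction).** The trial's hypothesis is that ECT relieves depression by enhancing slow waves and spindles. This places QIDS downstream of the sleep markers.

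**The concern.** A slope on treatment number answers Aims 1 and 2 only if nothing else in the model absorbs part of the course. Per-session QIDS is recorded after treatment starts and is expected to fall as treatment number rises. Among responders it must fall, because that is how the group is selected. Holding it fixed asks how SWA changes at constant depression severity, in people chosen because their severity halved. That is a different quantity from the one in the aims.

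Two features sharpen the problem. QIDS partly measures sleep, so it overlaps in content with the outcome. And if the sleep markers drive improvement, as the trial supposes, QIDS is a consequence of the outcome, and conditioning on a consequence biases the slope.

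At stake is the main result: a true rise in SWA or spindle density could be reported as null or, under some relationships, as a decline.

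**Working it through.** **1. The plan's own figure.** Inputs from Statistical analysis: partial η² 0.1, 10 treatments, power 0.8, alpha 0.05, 30% attrition. For a one-group repeated-measures F test, f² = 0.1/0.9 = 0.111, df1 = 9, df2 = 9(N − 1), λ = f² × N × 9. At N = 17, λ = 17.0 and power is 0.812, so 17 reproduces (two other noncentrality conventions give 16 and 18). Then 17/0.70 = 24.3, rounded up to 25. This calculation is for one group and has no covariates, so it does not describe the adjusted models.

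**2. Collinearity.** The documents give no QIDS trajectory or SD. Assume a 10-point linear fall over 10 sessions with session noise SD 2 to 3.

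- The variance of session numbers 1 to 10 is 8.25, and the fall per session is 10/9, so the trend variance is (10/9)² × 8.25 = 10.2.
- r² = 10.2/(10.2 + SD²), VIF = 1/(1 − r²), and standard-error inflation is √VIF.

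| Noise SD | r² | VIF | SE inflation |
|---|---|---|---|
| 2 | 0.72 | 3.55 | 1.9 |
| 3 | 0.53 | 2.13 | 1.5 |

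**3. What that does to power.** A separate simulation assumed 17 participants in one group, 10 sessions, a true slope of 0.10 residual SD per session, a QIDS fall of 1 point per session and QIDS SD 1.5 to 3 (VIF about 5.1 to 2.0). The unadjusted standard error is 1/√(17 × 82.5) = 0.027 and power is about 0.95 to 0.96. With per-session QIDS added and no effect shared with QIDS, the standard error is 0.060 to 0.038 and power is 0.39 to 0.74. The slope stays unbiased; only precision is lost.

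**4. If part of the course effect runs with QIDS.** Same simulation, true slope 0.10:

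| Share running with QIDS | Adjusted slope | Power |
|---|---|---|
| 0% | 0.10 | 0.39–0.74 |
| 25% | 0.075 | 0.24–0.50 |
| 50% | 0.05 | 0.12–0.24 |
| 75% | 0.025 | 0.07–0.11 |
| 100% | 0.00 | 0.05 |

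This treats all QIDS scatter around its trend as true mood variation. If only a fraction ρ of that scatter is true variation and the rest is measurement error, the adjusted slope is the total slope × (1 − share × ρ). With a share of 100%, ρ = 1 removes the slope and ρ = 0 leaves it intact. The documents give neither quantity, so the attenuation can lie anywhere from 0 to 100%.

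**5. If QIDS is downstream of the sleep marker.** Let QIDS fall c points per residual SD of SWA, with other QIDS noise of SD s and an overall fall of 1 point per session. Within participants the adjusted slope is 0.10 − c/(c² + s²).

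| c | s = 1.5 | s = 3 |
|---|---|---|
| 0.5 | −0.10 | +0.05 |
| 1 | −0.21 | 0.00 |
| 2 | −0.22 | −0.05 |

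Simulation gave the same values. At c = 1 and s = 1.5 the adjusted model rejected in over 99% of runs, in the wrong direction.

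**6. Where the problem is small.**

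- *Baseline QIDS.* It is constant within a participant and leaves the within-participant slope essentially unchanged.
- *Non-responders.* With a nearly flat QIDS (assumed 0.2 points per session, SD 3) and no shared effect, power moves only from 0.97 to 0.96. The collinearity cost falls mainly on the responder model.
- *Stimulation parameters.* A step at session 1 only, over 10 sessions, has r² = 0.45²/(0.09 × 8.25) = 0.27, VIF 1.38 and SE inflation 1.17.

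**The case against.** **The text does not say session-by-session, and its closing qualifier leaves room for judgement.** Both are true. A baseline-only score is possible and would be harmless, and a condensed article may leave covariate coding to a fuller document. That coding detail is absent is therefore not the point. The point is that the stated rule extends to all analyses, uses the plural for a score collected before every session, and sets no baseline restriction. Per-session entry is the likelier reading, and the qualifier leaves the choice between two estimands open.

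**A reader might infer that adjustment removes the course effect in every model.** The documents do not support this. Removal needs the whole effect to run with QIDS and the QIDS scatter to be true mood variation; nothing in the article establishes either. Nor does the argument carry directly to the exploratory CPC models, where treatment number is not the stated exposure.

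**A reader might place QIDS on the path from treatment to sleep EEG and conclude that the slope is simply pulled towards zero.** The Abstract's hypothesis runs the other way. Under it the distortion can go past zero.

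**A reader might treat the stimulation parameters as an equal fault.** This does not stand. Session-1 titration is described as typical for ECT-naïve individuals, later changes are conditional, and the Limitations section says montages may affect sleep markers differently. Adjustment for them can be defended as control of time-varying confounding.

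**Conclusion.** The point holds in a bounded form. As written, the covariate rule covers the Aim 1 and 2 models. If per-session QIDS is entered, the treatment-number slope estimates change at fixed depression severity and not the total change over the course.

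The precision loss is the firmer part: a 1.5- to 1.9-fold larger standard error, assuming a 10-point fall over 10 sessions and noise SD 2 to 3. It applies chiefly to responders. The bias cannot be sized from the documents: it may be nil, an attenuation of up to 100%, or a reversal of sign. Every slope, SD and QIDS trajectory used here is an assumption. The sample size of 17, with 25 recruited, is not in dispute.

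**What to change.** - **Primary Aim 1 and 2 models:** treatment number, with at most baseline QIDS as a covariate.
- **Labelled secondary model:** add per-session QIDS, split into the participant's mean and the within-participant deviation, to ask whether the sleep markers track mood beyond treatment number. Repeat it with the QIDS sleep items left out.
- **Sensitivity analysis:** stimulation parameters that change during the course.
- **CPC models:** state their covariates separately.

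The cost is analysis wording only, since the QIDS scores are already planned for collection at each session. The primary slope then describes the whole course as delivered, including any stimulation changes, and should be labelled that way.

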## Introduction

### Electroconvulsive therapy: An effective treatment for depression but with unclear underlying mechanisms

Electroconvulsive therapy (ECT) is an effective treatment for major depressive disorder (MDD), a common illness ranking as the second leading cause of disability worldwide (1). During ECT, a brief electrical stimulus is delivered through the scalp to elicit a generalized seizure under general anesthesia. Two to three ECT sessions are administered per week during the index treatment course. Compared to oral antidepressants, ECT ameliorates depressive symptoms rapidly; some individuals experience improvement shortly after the third treatment (2). The response rate to ECT for a depressive episode is up to 80% (2–4), with remission rates ranging from 50 to 63% (5, 6).

Electroconvulsive therapy was used for the first time on a human patient in 1938 by Cerletti and Bini (7). Although ECT has been used for over 80 years, many unknowns remain. It is thought that ECT induces neuroplasticity and alters neural connectivity within functional networks; however, these networks have yet to be elucidated (8, 9). Moreover, it remains unclear why certain patients do not respond to therapy. Prognostic physiologic biomarkers are not routinely used to predict and monitor ECT response. Identifying such biomarkers may aid clinicians in referring the right candidates for ECT or adapting ECT parameters (i.e., charge and electrode placement) to improve treatment response.

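### The 80% power stated for 17 participants belongs to an undivided sample, while the models the protocol specifies are fitted separately in responders and non-responders

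*Protocol article*

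**What the plan says.** The sample-size paragraph of the protocol article (Statistical analysis) gives its inputs as "We estimate a medium effect size and a partial η^2^ value of 0.1", "power of 0.8, alpha of 0.05", and a number of repeated measurements "based on a conservative assumption on the number of treatments (10 treatments"). From these it states "we estimate sample sizes of 17 (power of 0.8, alpha of 0.05"). The recruitment figure is for the study as a whole: "A total number of 25 participants will be targeted for recruitment in this study". With the 30% attrition seen in an earlier cohort at the same centre, the authors expect at least 17 participants with usable data. Response does not enter the calculation, and no size is given for either response group.

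The paragraph before it sets out the analysis. It describes mixed models of slow wave activity and of spindle density on treatment number, and then adds: "For all aims, separate models will be constructed for responder and non-responder groups". The Objectives and specific aims section repeats this separation for Aim 1, Aim 2 and the exploratory aim. Response is a 50% fall in the baseline QIDS score (Study design), so group sizes are known only after treatment. On the likely split, the Introduction says: "The response rate to ECT for a depressive episode is up to 80"%.

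**The concern.** A power statement should describe a test that will be run. Here the number is derived for all evaluable participants together, and the analysis is then specified in two subsets of them. Each subset is smaller than 17, and if ECT works as well as the Introduction suggests, the non-responder subset is very small.

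What is at stake is how the two sets of results are read. Under an advertised power of 0.8, a rise in slow wave activity in responders and no detected rise in non-responders could be taken as a difference linked to response. The same pattern could arise from group size alone. The Limitations section does not mention the split.

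**Working it through.** **Inputs.** From the Statistical analysis section: partial eta-squared 0.1, m = 10 treatments, alpha 0.05, target power 0.8, 25 recruited, 30% attrition. From the Introduction: response up to 80%. Assumed here: a lower response rate of 50%, complete data, and sphericity.

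**1. Is 17 a whole-study number?** 25 × 0.7 = 17.5, which matches the expectation of at least 17. In reverse, 17 / 0.7 = 24.3, rounded up to 25. It cannot be a size per response group.

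**2. Reproducing 17.**
- f² = 0.1 / (1 − 0.1) = 0.111.
- Within-subject F test in one group of n: df1 = m − 1 = 9, df2 = 9(n − 1), non-centrality λ = f² × n × 9 = n.
- n = 16: df2 = 135, λ = 16, power 0.781.
- n = 17: df2 = 144, λ = 17, power 0.812.

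So 17 is the smallest n that reaches 0.8. Other conventions come close but do not give 17: λ = f² × (n − 1) × 9 needs 18 (0.782 at 17), and λ = f² × n × 10 with zero correlation needs 16. The first formula with two groups and df2 = 9(N − 2) also gives 17 (power 0.810), but as a total for a pooled test.

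**3. The same formula after the split.**

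| Response rate | Group | Expected size | n used | Power |
|---|---|---|---|---|
| 80% | Responders | 17 × 0.8 = 13.6 | 13 to 14 | 0.66 to 0.71 |
| 80% | Non-responders | 17 × 0.2 = 3.4 | 3 to 4 | 0.13 to 0.18 |
| 50% (assumed) | Either group | 17 × 0.5 = 8.5 | 8 to 9 | 0.40 to 0.46 |

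At both ends of this range, each separate model falls short of 0.8.

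**4. Sensitivity to the type of test.** Step 2 is a 9-df test of any difference across 10 occasions. The planned models enter treatment number as an independent variable, which may mean a single slope. Apply partial eta-squared 0.1 to a 1-df slope with the full within-subject error df, so that df2 = 9n − 1 and λ = f² × (9n − 1):
- n = 3: df2 = 26, λ = 2.89, power 0.37.
- n = 4: df2 = 35, λ = 3.89, power 0.48.
- n = 8: df2 = 71, λ = 7.89, power 0.79.
- n = 9: df2 = 80, λ = 8.89, power 0.84.

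On this reading 9 participants suffice, so it does not yield the stated 17. If the slope is instead tested against between-subject df (λ = f² × n, df2 = n − 1), 73 participants are needed for 0.8.

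**The case against.** Three points on the other side have weight.

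First, a reader might infer that the 17 are never analysed together. The document does not go that far. The mixed models are first described without naming a group, and the hypotheses of Aims 1 and 2 (a rise over the course of ECT) are not group-specific. A pooled model is a possible reading, and the 0.8 would then apply to it. What stands is that no such model is stated, while the separate ones are, in both the aims and the analysis section.

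Second, a reader might infer that no planned test can have 80% power. That is not shown. On the 1-df slope reading in step 4, 9 or more responders could reach 0.8. The true power of the mixed models depends on variance components that the article does not give. Even so, 3 to 4 non-responders stay at about 0.37 to 0.48 on that reading. The criticism is therefore limited to the protocol's own calculation.

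Third, this is a single-centre observational study whose primary outcomes are described as characterization, and no confirmatory claim from a null result is planned. That lowers the stakes, but it does not make the printed power figure fit the printed models. A separate analysis plan could add detail, but the size and the models are both stated in this article and do not match.

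**Conclusion.** The point holds on the protocol's own calculation. The stated 0.8 describes an undivided sample of 17 and not the separate responder and non-responder models that the text specifies. Power per model is about 0.66 to 0.71 and 0.13 to 0.18 at 80% response, and about 0.40 to 0.46 in each group at 50% response.

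These figures assume complete data, sphericity and the F-test convention that returns 17. The 80% is the document's upper figure, and the 50% is assumed. The shortfall in a group of 3 to 4 non-responders persists under the more favourable slope reading. For responders the conclusion depends on which test was meant.

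The description of the effect as medium is not part of this point. The value used is printed, and the documents give no benchmark against which to judge the label.

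**What to change.** Name a full-sample mixed model, with all evaluable participants and optionally a treatment-number-by-response term, as the primary analysis of Aims 1 and 2. Say that the 0.8 refers to the full-sample change over treatments in that model (not to the response term), and whether that change is tested as a slope or as any difference across occasions. Report responder and non-responder slopes as descriptive estimates with confidence intervals. Restate the power per group over a 50% to 80% response range. If a pooled model was always intended, one sentence saying so settles the main question.

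The cost is wording in the analysis and sample-size paragraphs. The stated power becomes less favourable for the group-specific models. No more patients are needed. By contrast, securing 17 in the smaller group would take 17 / 0.5 = 34 evaluable (34 / 0.7 = 48.6, so 49 recruited) at 50% response, and 17 / 0.2 = 85 evaluable (85 / 0.7 = 121.4, so 122 recruited) at 80%.
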